### Quality Control

Before the trial, all staff will undergo special training on the purpose and content of the trial, treatment strategies, and quality requirements. Monitors will check the participant adverse event table, the participants’ lifestyle recommendation diary card, case report form, etc. once every week as well as the acupuncture operation during the treatment period. Dropouts and withdrawals and the underlying reasons will be documented in detail throughout the trial.

### Sample Size Calculation

In this study, change in 2hPG from baseline will be used as the basis for primary sample size estimation, based on the unpublished preliminary data collected from 10 participants in the acupuncture group and 10 SA group controls (-1.16 ± 0.42 mmol/L VS0.97 ± 0.34 mmol/L), and a sample size of 196 participants (98 per group) will need to provide the trial with 80% power with a two-sided significance level of 0.05 and 10% dropouts. The PASS 15 software was used for sample size calculation.

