## Introduction

Impaired glucose tolerance (IGT), measured by oral glucose tolerance test (OGTT), is an intermediate stage of hyperglycemia between normoglycemia and diabetes (1, 2). The latest research shows that 541 million adults, or 10.6% of adults worldwide, are suffering from IGT (3), with China as the top epicenter. Owing to the similar pathophysiological mechanism of insulin resistance (4–6), IGT is more commonly seen in people who are overweight/obese. The prevalence of IGT in people who are overweight/obese in China reached 46.6% in 2008 (7). If no intervention is administered, every year, about 7% of individuals with IGT will develop diabetes (8), which is deeply associated with many chronic and acute diseases (3, 9, 10). Meanwhile, vascular complications associated with type 2 diabetes mellitus (T2DM) could occur in the IGT stage, indicating increased risks of cardiovascular and cerebrovascular diseases, microvascular diseases, tumors, and dementia in the future (11–15). Additionally, both pre-diabetes (including IGT) and obesity, like diabetes, have been determined as risk factors for critical coronavirus disease 2019 (COVID-19) (16–18). These diseases tend to cause a great damage to organs, warrant long-term interventions, and require large costs, posing a great challenge to public health across the globe (19).

Fortunately, the hyperglycemia in IGT is reversible (20), which means it is possible to prevent or delay the development of diabetes. At present, the recognized effective interventions include lifestyle modifications and pharmaceuticals.

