### Outcome Measures

#### The Primary Outcome

The primary outcome will be change in the baseline value of 2hPG at the end of the 12-week treatment; 2hPG is the value of intravenous plasma glucose measured by 75 g OGTT, which is usually conducted to diagnose IGT and observe glucose metabolism (40). When the value of 2hPG fluctuates between 7.8 and 11.1 mmol/L, it will be regarded as IGT, and between 4.4 and 7.7 is the ideal control (40).

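### The stated 80% power does not follow from the 10-per-arm pilot it is based on: the printed figures give about 100%, a lost minus sign gives about 91%, and the pilot SD's own uncertainty spans 60% to 99%

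*Protocol article*

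**What the plan says.** The Sample Size Calculation section of the protocol article names change in 2hPG from baseline as the basis, "based on the unpublished preliminary data collected from 10 participants in the acupuncture group and 10 SA group controls". The pilot results are printed as "1.16 ± 0.42 mmol/L VS0.97 ± 0.34 mmol/L", with a minus sign before 1.16 and none before 0.97. The ± is not labelled there. From these figures the section arrives at "a sample size of 196 participants (98 per group"), for "80% power with a two-sided significance level of 0.05 and 10% dropouts".

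The section gives no other target difference, SD or allowance for the pilot's imprecision. The Primary Outcome section gives a category range for 2hPG ("When the value of 2hPG fluctuates between 7.8 and 11.1 mmol/L, it will be regarded as IGT") but no difference between groups that the trial is meant to detect.

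**The concern.** The section gives one power figure and one set of inputs, so a reader will take 80% as the chance of detecting the pilot difference if it is real. That difference and its SD both come from 20 people, and the sign of one mean is in doubt.

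The power figure frames how a non-significant result is read. If the true SD is near the upper end of what the pilot allows, the trial is clearly weaker than stated for a difference of 0.19 mmol/L. If the SD is near the pilot value, it is stronger than stated. If the printed difference of 2.13 is meant, the sample size bears no relation to the inputs. In each case the reader is misinformed about which differences the trial can and cannot rule out.

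**Working it through.** **Inputs** (Sample Size Calculation): change of -1.16 ± 0.42 for acupuncture and 0.97 ± 0.34 for sham, 10 per arm; two-sided alpha 0.05; power 80%; dropout 10%; 98 per arm. Completers per arm: 98 × 0.9 = 88.2, taken as 88. The ± is read as SD unless stated otherwise.

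**1. Pooled SD.** √((0.42² + 0.34²)/2) = √0.146 = 0.382.

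**2. Reproducing the stated N.** Normal formula: n per arm = 2 × (1.96 + 0.842)² × (SD/difference)².
- As printed, difference 0.97 − (−1.16) = 2.13: n = 0.5, rounded up to 1 per arm, or 2 after dropout.
- Sham read as -0.97, difference 1.16 − 0.97 = 0.19: n = 63.5, so 64 per arm (65 with the t distribution). After dropout this is 72 to 73 per arm, or 144 to 146 in total.

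Neither gives 98 per arm at 80% power.

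**3. Pilot difference.** SE = √(0.42²/10 + 0.34²/10) = 0.171; t(18) critical value 2.101.
- Difference 2.13: t = 12.5, 95% CI 1.77 to 2.49.
- Difference 0.19: t = 1.11, p = 0.28, 95% CI 0.19 ± 0.359 = -0.17 to 0.55.

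**4. Precision of the pilot SD.** Limits are √(18 × 0.146/χ²), with χ²(18) quantiles 31.53 and 8.23: 95% CI 0.289 to 0.565.

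**5. Power with 88 completers per arm** (two-sample t-test, noncentral t).

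| Difference | SD | Power |
|---|---|---|
| 2.13 (as printed) | 0.382 | about 100% |
| 0.19 | 0.289 | 99% |
| 0.19 | 0.382 | 91% |
| 0.19 | about 0.45 | 80% |
| 0.19 | 0.565 | 60% |

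If ± is a standard error, the SDs are 0.42 × √10 = 1.33 and 0.34 × √10 = 1.08, pooled 1.21. Power for 0.19 is then about 18%, and for 2.13 still about 100%.

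**6. What 88 per arm can detect.** 80% power corresponds to a standardised difference of 0.425. In mmol/L: 0.425 × 0.382 = 0.16; 0.425 × 0.565 = 0.24; 0.425 × 1.0 = 0.425. The SD of 1.0 is an assumption; the documents give no such figure.

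**7. Is an SD of change near 0.38 plausible?** With equal SDs at baseline and week 12, SD of change = baseline SD × √(2(1 − r)), so r = 1 − 0.146/(2 × baseline SD²).
- Baseline uniform over 7.8 to 11.1: SD = 3.3/√12 = 0.953, so r = 0.92.
- Baseline SD 0.5 (assumed): r = 0.71.

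**The case against.** Planning from a pilot is common, and power is always conditional on its assumptions. On the -0.97 reading, 196 participants give more than 80% power at the pilot SD and keep 80% up to an SD of about 0.45. The surplus over 146 may even be a deliberate margin: the one-sided 80% upper confidence limit of the pilot SD is 0.452, which needs 89 per arm, or 99 after dropout, close to 98. That is a fair point, but the section states no such margin and instead ties the 80% to the pilot data. The Statistical Analysis section reports normally distributed data as mean ± SD, so the SD reading is the more natural one. The pilot figures still need the label, given what the SE reading would do.

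Three stronger readings are tempting, and the documents do not support them.

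- A reader might infer that the pilot showed no effect. That holds only if 0.97 is changed to -0.97; the printed difference is far from zero.
- A reader might infer that an SD of 0.38 contradicts the 3.3 mmol/L entry window. The window limits baseline 2hPG, not its change. The required correlation depends on an assumed baseline spread, and no baseline SD or correlation is given.
- A reader might set the pilot SDs, under which almost nobody's 2hPG would rise, against the Introduction's statement that "about 7% of individuals with IGT will develop diabetes" each year. That rate is for people without intervention. Here both arms receive lifestyle recommendations, which the Introduction credits with reducing diabetes risk by more than half. The comparison also sets a far-tail extrapolation from 10 people per arm against a small event rate.

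**Conclusion.** The point stands in a limited form. The 80% figure is not supported by the inputs given for it. With 88 completers per arm, power is about 100% for the printed difference. For a difference of 0.19 it is 91% at the pooled pilot SD, and between 99% and 60% over that SD's 95% CI. It equals 80% only at an unstated SD of about 0.45.

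The 0.19 results assume a lost minus sign, and all of these figures assume that ± is an SD. Whether an SD of change near 0.38 is realistic for 2hPG is a plausibility concern, not a contradiction. It would also go too far to conclude that the trial is underpowered: on the -0.97 reading with the pilot SD it exceeds 80%, and power below 60% requires either the SE reading or an SD outside the pilot's 95% CI.

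**What to change.** Keep N = 196. In the Sample Size Calculation section:

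1. Confirm or correct the sign of the sham-group change.
2. Say whether ± is SD or SE.
3. Replace the claim of 80% power for the pilot difference with a statement that 88 completers per arm give 80% power, at two-sided 0.05, for a standardised difference of 0.425. Add its size over a range of SDs: 0.16 mmol/L at SD 0.38, 0.24 at 0.57 and 0.425 at an assumed SD of 1.0. These values do not depend on the sign. If ± proves to be SE, re-centre the SD range on the corrected value.

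The cost is a few lines of text, with no extra participants and no change to the analysis. The drawback for the sponsor is that the stated figure may look less favourable.

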**Methods:**

The trial will be conducted at hospitals in three different sites in China. A total of 196 participants will be recruited and randomly assigned at a ratio of 1:1 to either to the acupuncture group or the sham acupuncture (SA) group. Both groups will receive 30 sessions of treatment for 12 consecutive weeks and will be provided with lifestyle intervention and a 24-week follow-up. The primary outcome will be change in the baseline value of 2-h blood glucose (2hPG) on the 12th week. Additionally, the expectancy of acupuncture, blinding, and safety will also be assessed. All statistical analyses will be performed by two-sided test, and a *p*-value of less than 0.05 will be considered statically significant.

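### The 196 participants stated for 80% power cannot be reproduced from the difference and SDs printed in the sample size paragraph

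*Protocol article*

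**What the plan says.** All the inputs stand in one paragraph of the protocol article, under Sample Size Calculation.

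- Endpoint: "change in 2hPG from baseline will be used as the basis for primary sample size estimation".
- Source: "unpublished preliminary data collected from 10 participants in the acupuncture group and 10 SA group controls".
- Values: "1.16 ± 0.42 mmol/L VS0.97 ± 0.34 mmol/L". A minus sign stands before 1.16, and none before 0.97.
- Error rate and attrition: "two-sided significance level of 0.05 and 10% dropouts".
- Result: "a sample size of 196 participants (98 per group) will need to provide the trial with 80% power", computed in PASS 15.

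The abstract adds that participants are "randomly assigned at a ratio of 1:1". The Statistical Analysis section presents normally distributed data as mean ± SD, so I read the ± values as SDs. The article gives no other difference, SD or design factor for the sizing.

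**The concern.** The paragraph prints a full set of inputs and a result, so a reader can repeat the calculation, and the result does not come out.

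Two things are at stake. First, this is the only justification of size for the primary outcome, and its power figure does not match its own inputs. Second, the effect the trial was designed to detect is unclear. As printed, 2hPG rises by 0.97 mmol/L under sham and the design difference is 2.13 mmol/L. With a minus sign before 0.97 it is 0.19 mmol/L, about eleven times smaller (2.13 / 0.19 = 11.2). Anyone who later compares the observed effect with the planned one needs to know which was meant.

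**Working it through.** **Inputs** (Sample Size Calculation, except allocation, from the abstract)

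- Mean changes: −1.16 (acupuncture) and 0.97 (sham, sign in question) mmol/L
- SDs: 0.42 and 0.34 mmol/L
- Two-sided α 0.05, power 80%, dropout 10%, allocation 1:1
- Stated result: 98 per group, 196 in total

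**Formulas**

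- Pooled SD = √[(0.42² + 0.34²)/2] = √[(0.1764 + 0.1156)/2] = √0.146 = 0.382.
- Approximate size per arm: n = 2(1.96 + 0.842)² SD² / difference². The sizes below are exact for a two-sample t-test (noncentral t).
- Enrolled per arm = n / 0.9, rounded up. Multiplying by 1.10 instead changes the totals below by at most 2.
- Evaluable per arm with 98 enrolled = 98 × 0.9 = 88.2, taken as 88.

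**Attempt to reproduce 196 at 80% power**

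*Sham change −0.97 (a minus sign was lost).* Difference = 1.16 − 0.97 = 0.19. The approximation gives 2 × 7.85 × 0.146 / 0.0361 = 63.5, so 64 per arm. The exact t-test needs 65. Then 65 / 0.9 = 72.2, so 73 per arm and 146 in total.

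*Sham change +0.97 (as printed).* Difference = 1.16 + 0.97 = 2.13. The exact t-test needs 3 per arm (power is 79% with 2 and over 99% with 3). Then 3 / 0.9 = 3.3, so 4 per arm and 8 in total.

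| Difference | SD | Power | Evaluable per arm | Enrolled per arm | Total |
|---|---|---|---|---|---|
| 2.13 | 0.382 pooled | 80% | 3 | 4 | 8 |
| 0.19 | 0.382 pooled | 80% | 65 | 73 | 146 |
| 0.19 | 0.42 both arms | 80% | 78 | 87 | 174 |
| 0.19 | 0.34 both arms | 80% | 52 | 58 | 116 |
| 0.19 | 0.382 pooled | 90% | 86 | 96 | 192 |
| Stated | | 80% | | 98 | 196 |

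No 80% row gives 196. The nearest row is the one for 90% power, which is not the stated power.

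**Power that 196 gives at a difference of 0.19**

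- 88 evaluable per arm, pooled SD 0.382: noncentrality = 0.19 / (0.382 × √(2/88)) = 3.30, power 90.7%.
- All 98 per arm evaluable, pooled SD 0.382: 93.4%.
- 88 evaluable per arm, SD 0.42 in both arms: 84.7%.

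At a difference of 2.13 the power is essentially 100%.

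**What would make 80% correct at 88 evaluable per arm**

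- Difference 0.19 with a common SD of 0.447, about 0.45; or
- Pooled SD 0.382 with a difference of 0.162.

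The paragraph states neither.

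**The case against.** Four points can be made for the plan.

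1. *The sign may be a text artefact.* The sham value follows VS without a space, just where a minus sign would stand, and a character could have been lost in typesetting or in reading the PDF. This stands. The sign cannot be settled from the text available, so it should be verified rather than declared wrong. The mismatch does not depend on it, because −0.97 does not give 196 either.

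2. *80% may be right, with an input left unstated.* The size is said to be based on the pilot, which does not mean that the raw pilot SDs were entered. The one-sided 80% upper confidence limit for the pilot SD is about 0.45. With 0.452 the t-test needs 90 evaluable per arm, and 90 / 0.9 = 100 per arm, or 200 in total, within about 2% of 196. A rank-test adjustment with SD 0.42 in both arms gives roughly 182 to 202 in total, depending on the adjustment. This also stands in part. A reader might infer that the stated power is simply false. The documents do not support that, because an undisclosed conservative input could make it true. They support only that the figure does not follow from the inputs given.

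3. *A condensed article may leave PASS settings to the full protocol.* That would excuse silence. It does not excuse printing inputs beside a result they do not produce.

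4. *Nothing is lost in practice.* At a difference of 0.19 with the printed SDs, 196 is more than 80% power requires. This is right, and it limits the point to a reporting correction. A reader might go the other way and infer from the small pilot that the trial is underpowered. How well 10 per arm pins down the SD is a separate question about planning assumptions, and this arithmetic does not show a shortfall.

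**Conclusion.** The point holds in this form: 196 participants for 80% power at two-sided 0.05 with 10% dropout is not reproducible from the printed inputs.

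On the more plausible reading, a sham change of −0.97, those inputs call for 146, so the stated number is 50 higher (34%). The 91% for 196 rests on three conditions: the minus sign was lost, the pilot SDs of 0.42 and 0.34 apply, and 88 per arm are evaluable. It falls to about 85% if SD 0.42 is used in both arms. The lost minus sign is an inference, supported by the spacing in the text and by 196 lying close to the 90%-power result for 0.19. Reading ± as SD follows the convention in the Statistical Analysis section.

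The defect is a power statement and a design effect that cannot be traced. The number to be recruited is not shown to be too small.

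**What to change.** Rewrite the one paragraph and keep 196.

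1. Verify the sign of the sham change against the pilot data, and correct it if needed.
2. State the difference and the SD actually entered in PASS.
3. Make the power agree with them. If 0.19 and SDs of 0.42 and 0.34 were entered, restate the power as about 91% with 88 evaluable per arm. If a larger SD or a smaller difference was entered, state that value and keep 80%.

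The cost is one corrected paragraph, with no change to sample size, conduct or analysis.

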### Statistical Analysis

We will use the SPSS V.25 software (IBM Corp., Armonk, NY, United States) to perform all statistical analyses following the intention-to-treat principle. CI will be established at 95% and significance level at 0.05. Missing data will be calculated using the actual observational value without imputation if the dropout rate is no more than 5%. For continuous data, the data will be presented as mean ± *SD* if normally distributed or as median (IQR) if not normally distributed. Longitudinal continuous data will be compared between the groups by repeated-measures analysis of variance (ANOVA) including group and time–group interaction. Other continuous data will be analyzed by Student’s *t*-test and Wilcoxon rank-sum test, and categorical data by X ^2^ test or Fisher’s exact test, as appropriate. Linear correlation analysis will be conducted to measure the closeness of linear correlation between variables. Sensitivity analysis will be performed if necessary. A *p*-value < 0.05 will be considered statistically significant.

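### The only missing-data rule stops at 5% dropout although the trial is sized for 10%, and repeated-measures ANOVA, if used for 2hPG, would discard week-12 values of participants who miss a later visit

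*Protocol article*

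**What the plan says.** All references are to the protocol article.

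- **Statistical Analysis, missing data.** The single rule is "Missing data will be calculated using the actual observational value without imputation if the dropout rate is no more than 5" (per cent). Nothing is stated for a higher rate. A sensitivity analysis is left to be done only if it is felt to be needed.
- **Statistical Analysis, principle.** SPSS V.25 is to be used "to perform all statistical analyses following the intention-to-treat principle".
- **Statistical Analysis, model.** "Longitudinal continuous data will be compared between the groups by repeated-measures analysis of variance (ANOVA) including group and time–group interaction". The remaining continuous data go to the t-test or the rank-sum test. The text does not say which of the two routes the primary outcome takes.
- **Sample Size Calculation.** The 196 participants, 98 per group, are to give "80% power with a two-sided significance level of 0.05 and 10% dropouts".
- **Outcome Measures.** The primary outcome is the change in 2hPG from baseline to week 12. The changes at weeks 24 and 36 are secondary. 2hPG is therefore measured at baseline and three times afterwards.

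**The concern.** There are two linked problems.

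First, the missing-data rule is switched on by the dropout rate that turns out, and the switch is set at half the rate the trial was planned for. At the planned rate the article says nothing about how missing 2hPG values are handled. This goes beyond detail left to an analysis plan, because the article does fix a rule, and that rule does not fit its own planning assumption.

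Second, repeated-measures ANOVA in its usual form (the general linear model procedure in SPSS) needs a value at every visit and deletes a participant who lacks one. If it is the model for 2hPG, whether a week-12 result counts would depend on attendance up to 24 weeks after treatment ended. That selects participants on something that happens after randomisation, which an intention-to-treat analysis is meant to avoid.

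**Working it through.** **Inputs.** From Sample Size Calculation: N = 196 (98 per group), 10% dropout, 80% power, two-sided 0.05, and pilot changes printed as "1.16 ± 0.42 mmol/L VS0.97 ± 0.34 mmol/L" with a minus sign before the first value only. From Statistical Analysis: the 5% threshold. From Outcome Measures: 2hPG at weeks 12, 24 and 36.

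**1. The plan's own figure.** With pooled SD = √((0.42² + 0.34²)/2) = 0.382 and n = 2(1.96 + 0.84)² × SD²/d²:
- Difference as printed, d = 1.16 + 0.97 = 2.13: n is about 1 per group by this approximation.
- d = 1.16 − 0.97 = 0.19, assuming that both means are negative: n = 64 per group, and 64/0.9 gives 72 after dropout, 144 in total.

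Neither gives 196. That is a separate issue. Here 196 and 10% are taken as stated.

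**2. Does the rule cover the planned case?**
- Expected dropouts: 0.10 × 196 = 19.6, leaving about 176 (88 per group).
- Most dropouts allowed by the rule: 0.05 × 196 = 9.8, so 9 (9/196 = 4.6%).
- Chance of 9 or fewer dropouts among 196 (binomial, participants independent):

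| True dropout rate | Chance that the rule applies |
|---|---|
| 5% | 0.48 |
| 8% | 0.044 |
| 10% (planned) | 0.0045 |
| 12% | 0.0003 |

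**3. What would listwise deletion remove?** This step applies only if 2hPG goes into a repeated-measures ANOVA run in the usual way on unimputed data.
- Permanent dropout of 10% and no other missed visits: about 176 of 196 are complete, the number planned for. Anyone who left after week 12 had a week-12 value that is thrown away.
- The same 10%, plus a further share m of values missed independently at each of the three later visits (assumption): 196 × 0.9 × (1 − m)³ gives 166 for m = 2% and 151 for m = 5%.
- Stronger assumption, 10% missed independently at each visit: 0.9³ = 0.729, and 98 × 0.729 is about 71 per group, against 88 with a week-12 value. For d = 0.19 the power (Welch t-test) is 0.906 with 88 per group and 0.837 with 71.

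**4. What would informative dropout do?** Suppose that 10% are lost in one group only and that their change is 1 mmol/L worse than that of completers (both assumptions). The estimate shifts by 0.10 × 1 = 0.10 mmol/L. That is 0.10/0.19 = 53% of the smaller reading of the planned difference, or 0.10/2.13 = 5% of the difference as printed. A gap of 1 mmol/L is 1/0.42 = 2.4 to 1/0.34 = 2.9 of the pilot SDs, so this is an extreme case.

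**The case against.** A reader might infer that the primary comparison is restricted to participants who completed 36 weeks, and that the plan therefore openly contradicts intention-to-treat. The documents do not support this.

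- **The primary test is not named.** The primary outcome is a change at a single time point, so it may fall under the t-test route. A missed week-24 or week-36 test would then remove nobody from it.
- **Listwise deletion is not written down.** It is the usual behaviour of the named method, but no SPSS procedure is given. No sentence excludes dropouts, and the Rescue Medication section keeps participants who take other treatment in the study.
- **Imputation may be intended above 5%.** A rule of no imputation up to 5% suggests imputation beyond it. If so, there would be few incomplete cases left to delete at the planned rate, and the choice of imputation method could reasonably sit in a fuller document.
- **The numbers are illustrations.** The 73% retention needs 10% missing independently at every visit, whereas the plan speaks of 10% dropouts overall. Even then power is 84%, above the stated 80%. The 0.10 mmol/L shift is a not-at-random bias, which a mixed model alone would not remove, so it says nothing against ANOVA in particular.

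All of this stands, and it makes the ANOVA point conditional. It does not close the gap between 5% and 10%. Imputation above 5% is a guess from the wording, and even if it is right, the method would still switch on an observed rate.

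**Conclusion.** The mismatch is on the page and needs no outside figure: at the planned 10% dropout the only stated rule would apply with a probability of about 0.005, and the article names nothing in its place. This holds whichever test is primary.

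The second part is conditional. If repeated-measures ANOVA covers 2hPG and is run in the usual way, valid week-12 values are lost through later missed visits, which does not fit intention-to-treat. If a t-test is used for week 12, that loss does not arise.

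The size of any bias or power loss cannot be determined from the documents. It depends on the pattern and reasons of missed visits, and on whether the planned difference is 0.19 or 2.13 mmol/L. The point is worth correcting because it concerns the primary outcome and has to be settled before dropout is known. A large distortion has not been shown.

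**What to change.** 1. Delete the 5% switch, so that one method holds at any dropout rate.
2. State the primary analysis: the week-12 between-group contrast from a likelihood-based mixed model for repeated measures on change in 2hPG at weeks 12, 24 and 36, with group, visit and their interaction, using all randomised participants with any post-baseline 2hPG. A missed later visit then no longer removes a week-12 value.
3. Pre-specify one sensitivity analysis for data not missing at random and run it always. An example is multiple imputation for all randomised participants with a delta shift, over a range of shifts set before unblinding. This also brings in those with no post-baseline value, and it addresses the bias that the mixed model alone would leave.

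Other methods valid at any dropout rate could serve. What matters is that the choice is named and does not depend on the dropout seen. The cost is a few sentences and a little more analysis work, with no extra participants or visits.

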#### Secondary Outcomes

(1) Change from baseline value of 2-h blood glucose on weeks 24 and 36.

(2) Proportion of participants whose 2-h blood glucose dropped to normal from baseline on weeks 12, 24, and 36.

(3) Proportion of participants with at least 5% reductions (47) in body weight from baseline on weeks 4, 8, 12, 16, 24, and 36.

(4) Change from baseline of body mass index (BMI) and waist-to-hip ratio (WHR) on weeks 4, 8, 12, 16, 24, and 36.

(5) Change from baseline of fasting plasma glucose (FPG), fasting serum insulin (FINS), homeostasis model assessment-insulin resistance index (HOMA-IR), TC (serum total cholesterol), TG (triglyceride), LDL-C (low-density lipoprotein cholesterol), and high-density lipoprotein cholesterol (HDL-C) on weeks 12, 24, and 36.

(6) Change from baseline of blood pressure on weeks 12, 24, and 36.

(7) Change from baseline in the Impact of Weight on Quality of Life-Lite Questionnaire (IWQOL-Lite) scores on weeks 4, 8, 12, 16, 24, and 36.

IWQOL-Lite is an international scale used to measure an individual’s health-related quality of life (48). A total of 31 questions are divided into five subscales: 11 questions concerning physical function, 7 concerning self-esteem, 4 concerning sex life, 5 concerning public pressure, and 4 concerning work. The score of each question is divided into five grades, with 5 representing always, 4 often, 3 sometimes, 2 rarely, and 1 never. The total score of the questionnaire is 155, with higher score indicating worse quality of life. The MCID of IWQOL-Lite is 12 (49) for overweight/obesity.

(8) Change from baseline in the Simplified Nutritional Appetite Questionnaire (SNAQ) scores on weeks 4, 8, 12, 16, 24, and 36.

The SNAQ scale is a short and simple appetite assessment tool that can predict weight loss in adults (50). It measures the amount of food per meal, the number of meals per day, and the taste of the food. It consists of four items, each with five grades and with the total score ranging from 4 to 20 points. Lower scores indicate deterioration in appetite (50).

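### The primary outcome is the week-12 change in 2hPG, but the rule that most directly covers it is a repeated-measures ANOVA whose group and interaction terms do not estimate that difference

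*Protocol article*

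**What the plan says.** The protocol article fixes the primary endpoint at one time point (The Primary Outcome): "The primary outcome will be change in the baseline value of 2hPG at the end of the 12-week treatment". The same measurement returns as a secondary outcome: "Change from baseline value of 2-h blood glucose on weeks 24 and 36". With the baseline value, 2hPG is therefore taken at four times: baseline and weeks 12, 24 and 36.

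The Statistical Analysis section assigns tests by type of data, not by outcome. One rule reads: "Longitudinal continuous data will be compared between the groups by repeated-measures analysis of variance (ANOVA) including group and time–group interaction". The rule for what remains reads: "Other continuous data will be analyzed by Student’s *t*-test and Wilcoxon rank-sum test". The section does not say which rule governs the primary outcome, or which term of the ANOVA would carry the primary claim.

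The Sample Size Calculation rests on a two-group comparison: "change in 2hPG from baseline will be used as the basis for primary sample size estimation". Its inputs are two means and SDs of change.

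**The concern.** 2hPG is a continuous variable measured repeatedly, so the longitudinal rule is the direct reading. That rule answers different questions from the one the primary outcome asks.

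- **Group term.** It compares the arms on the average over the visits entered. Weeks 24 and 36 lie in the follow-up, after the last needling session. If raw values are analysed with baseline as a level, the average also includes a visit at which randomisation makes the expected difference zero.
- **Time-group interaction.** It asks whether the difference between arms varies across visits at all. It does not say at which visit, or in which direction.

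At stake is the trial's main test. Depending on the term used, a real week-12 effect could go undetected, or a significant result could arise with no effect at week 12. With two F-tests, and raw values or changes as possible inputs, the article leaves several candidate p-values for one primary question.

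**Working it through.** **Inputs from the article**
- Changes (Sample Size Calculation): "1.16 ± 0.42 mmol/L VS0.97 ± 0.34 mmol/L", with a minus sign printed before 1.16 and none before 0.97. As printed the difference is 1.16 + 0.97 = 2.13 mmol/L. If a minus sign was lost before 0.97, it is 1.16 − 0.97 = 0.19.
- Pooled variance of change: (0.42² + 0.34²)/2 = 0.146, so SD = 0.382.
- Size: "98 per group) will need to provide the trial with 80% power with a two-sided significance level of 0.05 and 10% dropouts". Completers per arm: 98 × 0.9 = 88.
- Allocation: "randomly assigned at a ratio of 1:1".

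**The plan's own figure.** With 0.19, n per arm = 2(1.960 + 0.842)² × 0.146/0.19² ≈ 64 (65 by the t distribution), or 72 to 73 after dropout, 144 to 146 in total. With 2.13, 1 to 3 per arm suffice. Neither gives 196; 90% power with 0.19 gives 190 to 194. This is a separate matter and does not affect the present point.

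**Assumptions for the illustration.** Difference 0.19; compound symmetry with correlation ρ of 0.3, 0.5 or 0.7; two-sided 0.05. Then the variance of a single value is σ² = 0.146/(2(1 − ρ)).

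**Formulas**
1. *Direct week-12 comparison of change:* noncentrality 0.19/√(2 × 0.146/88) = 3.30 on 174 df; power 0.91.
2. *Group term, raw values at four visits:* the variance of a participant's mean is σ²(1 + 3ρ)/4. For an effect at week 12 only, the term estimates 0.19/4 = 0.0475. At ρ = 0.5, σ² = 0.146 and the variance is 0.0912, so the noncentrality is 0.0475/√(2 × 0.0912/88) = 1.04; power 0.18.
3. *Interaction, raw values:* the error variance σ²(1 − ρ) = 0.073 does not depend on ρ. λ = 88 × Σ(d − d̄)²/(2 × 0.073) on 3 and 522 df. For week 12 only, Σ(d − d̄)² = 0.0271, λ = 16.3; power 0.94. For weeks 24 and 36 only, Σ(d − d̄)² = 0.0361, λ = 21.8; power 0.98.
4. *Change scores at weeks 12, 24 and 36:* compound symmetry makes any two changes correlate at 0.5 whatever ρ is. The variance of the mean of three changes is 0.146 × 2/3 = 0.0973. The interaction has 2 and 348 df.

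**Rejection probabilities**

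| True difference at baseline, 12, 24, 36 | Direct week 12 | Group, raw (ρ 0.3 / 0.5 / 0.7) | Interaction, raw | Group, change | Interaction, change |
|---|---|---|---|---|---|
| 0, 0.19, 0, 0 | 0.91 | 0.29 / 0.18 / 0.11 | 0.94 | 0.27 | 0.93 |
| 0, 0.19, 0.095, 0 | 0.91 | 0.56 / 0.34 / 0.19 | 0.91 | 0.52 | 0.85 |
| 0, 0.19, 0.19, 0.19 | 0.91 | 0.99 / 0.88 / 0.58 | 0.94 | 0.98 | 0.05 |
| 0, 0, 0.19, 0.19 | 0.05 | 0.80 / 0.55 / 0.30 | 0.98 | 0.76 | 0.93 |

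A simulation of 4000 trials per scenario at ρ = 0.5 agrees: for the first row it gives 0.90 to 0.91 (direct), 0.16 and 0.26 (group, raw and change) and 0.93 (interaction, raw and change).

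**With the printed 2.13.** For an effect at week 12 only, the direct comparison and both ANOVA terms have power of about 1.

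**The case against.** The strongest reply is that the article never ties the primary outcome to the ANOVA. One week-12 change score per participant can be read as belonging to the remaining continuous data, which get a t-test or Wilcoxon test. The sample size, built on two means and SDs of change, fits that reading. This stands: a reader might infer that the article prescribes the ANOVA as the primary analysis, and it does not say so. But it does not say the t-test applies either, and the wording for longitudinal data describes 2hPG more directly.

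A second reply is that contrasts and decision rules are commonly left to the analysis plan. That is fair for detail. Here, however, the article states a rule which, on its direct reading, does not match the endpoint that it also states. The remedy corrects existing text.

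A third reply concerns size. A reader might infer from the group term's 11 to 29% that the trial would lose most of its power. That holds only if the group term decides. The raw-value interaction does as well as the direct test for a week-12-only effect (0.94 against 0.91). The 0.19 is itself an assumption, and no loss appears for that pattern with the printed 2.13. The late-effect scenario is also only an illustration; nothing in the article predicts it.

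Finally, the Blinding section says that the statisticians are blinded to allocation, so a choice of test made with knowledge of the arms is not a supported charge. The blinding does not say which of the candidate tests is primary.

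**Conclusion.** The point holds as a mismatch between endpoint and test on the most direct reading of the Statistical Analysis section, left unresolved by the rest of the article. The group term estimates an average over visits and the interaction is an omnibus test; neither yields the week-12 difference or its confidence interval. This part rests on no numerical assumption.

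The size does. With 0.19, 88 per arm, SD 0.382 and compound symmetry, power for a week-12-only effect runs from 0.11 to 0.94 across the raw-value ANOVA terms, against 0.91 for the direct comparison. With no week-12 effect but 0.19 later, the raw-value terms reject in 30 to 98% of trials although the primary null hypothesis is true. The documents do not support the stronger claims that the ANOVA is fixed as the primary analysis or that the trial is underpowered because of it.

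**What to change.** Add to the Statistical Analysis section that the primary test is the between-group difference in 2hPG change at week 12, reported with its 95% CI and adjusted for baseline 2hPG. It can come from a week-12 ANCOVA or from the week-12 contrast of a mixed model for repeated measures. State also that weeks 24 and 36 are secondary, and that the group main effect and the omnibus interaction carry no primary claim.

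The cost is two sentences. The data, the visits and the SPSS software stay the same. If the t-test rule was always meant for the primary outcome, saying so would remove the ambiguity; the baseline-adjusted version answers the same question and uses the baseline value already collected.
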